### Aim 2: assessment of acceptability and feasibility

The *primary implementation outcome* to be assessed is the uptake of each of the two interventions. VPHC data will be collated weekly, and CC data will be collated monthly.

*VPHC*: the primary outcome will be the number of referrals made. This will be monitored via the ePJS form and a database designed by the IMPHS team to document referrals. This form will include details of referrer, ward and purpose of the referral.

*CC*: the primary outcome will be the number of calls made*.* These data will be derived from routinely collected CC data.

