#### Study aims

The primary aim of the evaluation is to understand the process of rapidly implementing the VPHC and CC. This formative evidence on the implementation of both services will ensure that implementation can be rapidly optimised and supported in the long-term.

The secondary aim of the evaluation is to establish the acceptability and feasibility of both the VPHC and CC.

The tertiary aims of the evaluation are to:
Undertake an exploratory analysis to inform future roll out and impact evaluation through establishing the likely patient benefit of the interventions and developing a logic model. Through monitoring the types of referrals and contacts with CC and VPHC, evidence will be gathered on the likely effect of the interventions. For example, the exploratory phase will enable testing of whether it is plausible to expect the interventions to improve the management of long-term conditions such as diabetes.Conduct an economic evaluation including initial cost comparison to establish if the interventions are plausibly cost neutral or cost saving and to view this evidence in light of likely patient benefit (or whether VPHC and CC are likely to at least deliver equivalent patient outcomes compared to usual care), without evidence of any detrimental effects, and acceptability to staff.

Initial assessments will inform decision-making regarding the longer term (i.e. post-COVID-19 crisis response) implementation and sustainability of these interventions. We will also evaluate any inequalities in the use of the service by investigating referrals for different demographic groups.

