### Implementation of VPHC and CC in SLaM during COVID-19 pandemic

#### VPHC

VPHC is accessed using a brief referral form on the electronic healthcare record—ePJS—which will ask for details of the referrer and what the referral is being made for. Each referral request will be triaged by IMPHS project clinical staff and the King’s College Hospital (KCH) Consultant, and the referrer will be offered either a virtual appointment for the referrer (with patient present) or telephone advice for referrer only. Where appropriate to do so, referrals will be signposted onwards. The process will be documented and monitored by the IMPHS Team to ensure referrals are actioned in a timely manner. All appointments will be conducted using phone or Microsoft Teams software, providing a discussion between the KCH consultant, the referrer and the patient. The advice and discussion will be recorded on ePJS by the referring clinician.

The VPHC will be trialled on the Maudsley site initially to test the systems and ascertain the level of use. Having quantified the referral rate over the initial 9-month trial and if the system is working successfully, the VPHC will be rolled out across further SLaM adult inpatient sites subject to agreement of resource.

The process for the VPHC is set out in Fig. 2.

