### Implementation data analysis

Contextual factors will be documented throughout roll out such as ongoing changes to SLaM ward configurations in response to infection prevention and control guidelines or any changes to services provided by local Acute Trusts. This contextual data will be used to understand external influences on the uptake of the VPHC and CC and the running of the VPHC.

For our primary implementation assessment, data on implementation strategies applied will be collected and a descriptive analysis conducted, categorised by service (VPHC and CC). The number and type of strategies used will be recorded. Precisely how the strategies were implemented will be described qualitatively and any shifts in strategies over time also recorded.

For our secondary implementation assessment, a descriptive analysis will be conducted for both services for the primary (measured as number of referrals being made for VPHC on a monthly basis and number of calls being made for CC on a weekly basis), secondary (measured as number of appointments, reasons of appointments and access to internal triage) and implementation outcomes. In order to monitor primary and secondary outcomes, descriptive graphs and Statistical Process Control charts will be employed on weekly and monthly basis.

For our tertiary implementation assessment, standardised implementation survey outcomes (AIM, IAM, FIM) will be assessed via a descriptive statistical analysis. Difference in the total scores of implementation survey outcomes by service (VPHC vs CC) and within each service over time (to capture any effects of different implementation strategies) will be assessed with the use of generalised regression models (Poisson or linear depending on the distribution of the outcome).

As the evaluation design is formative, outcomes will be analysed and fed back to SLaM via the Physical Health Implementation Committee and the IMPHS steering group, and this will be provided in an easily understood usage report. This will allow adjustments to be made to the implementation process of both interventions.

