#### Quantifying impact on wider healthcare utilisation

Data will be analysed from available datasets to establish a baseline level of healthcare utilisation to inform the cost comparison scenario analysis. We will collect data from the year before the VPHC and CC begin and during the pandemic. The following data will be evaluated for baseline estimation and ongoing monitoring:
Number of referrals/attendances to Emergency Departments (ED) or other Acute Trust services per month before and during the roll out.Length of stay in ED or Acute Trust wards before and during roll out.Length of stay on SLaM wards before and during roll out.

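### Uptake and monthly acute-care use are defined as counts without a denominator while the number of inpatients covered may change, so shifts may partly reflect coverage; bed-day rates should be added

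*Protocol article*

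**What the plan says.** **Uptake.** Under Aim 2, for VPHC "the primary outcome will be the number of referrals made" and for CC "the primary outcome will be the number of calls made". The section Implementation data analysis repeats this: VPHC uptake is "measured as number of referrals being made for VPHC on a monthly basis", CC uptake is again a number of calls per period, and "descriptive graphs and Statistical Process Control charts will be employed on weekly and monthly basis". The type of control chart, for counts or for rates, is not stated.

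**Acute-care use.** The first item under Quantifying impact on wider healthcare utilisation is "Number of referrals/attendances to Emergency Departments (ED) or other Acute Trust services per month before and during the roll out". The baseline is the year before the services began. The other two items are lengths of stay.

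**Coverage.** Implementation data analysis expects "ongoing changes to SLaM ward configurations in response to infection prevention and control guidelines" and will record them as context. According to Setting, VPHC starts on one site and CC is offered to all inpatient services. VPHC may be extended to further sites, and CC to community teams.

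**Quantities that imply a denominator.** The Abstract announces data on reach. The VPHC section makes wider roll-out follow a step worded "Having quantified the referral rate over the initial 9-month trial". Cost comparison scenario analysis intends an overall risk of attendance or admission. None of these places names the population at risk.

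**Inequality.** Study aims says the team will "evaluate any inequalities in the use of the service by investigating referrals for different demographic groups". It gives neither a scale nor a comparison population.

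**The concern.** A count per month is the product of use per inpatient and the number of inpatients. If wards are merged, closed, opened or repurposed, or if sites are added, the second factor moves and the count moves with it, even when clinicians refer exactly as often per patient as before.

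The counts are acted upon. Implementation strategies are to be reviewed in the light of uptake, usage reports are meant to prompt adjustments, and VPHC roll-out follows the quantified referral figure. A change in coverage could be taken for a strategy working or failing. The ED and Acute Trust series sets a pre-service year against pandemic months, a contrast in which the inpatient population may well differ.

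For the inequality aim, the number of referrals from a group says little until it is set against how many inpatients belong to that group.

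**Working it through.** **1. What can be reproduced.** The article gives no bed numbers, admissions, expected counts or demographic mix. There is no figure to reproduce, and no corrected figure can be derived. What follows is an identity and an illustration with assumed inputs.

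**2. The identity.** Count = (use per bed-day) × (occupied bed-days). Hold use per bed-day constant and multiply bed-days by *f*. The count then changes by (*f* − 1): −40% at *f* = 0.6, −20% at 0.8, +20% at 1.2, +50% at 1.5. The rate ratio is 1.0 throughout.

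**3. Effect on a control chart.** Assume Poisson monthly counts, a count chart with centre *c* and limits *c* ± 3√*c*, and nine monthly points (the length of the initial VPHC trial). If *p* is the chance that one point falls outside the limits when the true mean is *c* × *f*, the chance of at least one such point is 1 − (1 − *p*)⁹.

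Example: *c* = 40 gives limits 40 ± 18.97, that is 21.03 to 58.97. With *f* = 0.8 the mean is 32 and *p* = 0.026, so 1 − 0.974⁹ = 0.21.

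| Assumed mean *c* | *f* = 0.6 | *f* = 0.8 | *f* = 1.0 | *f* = 1.2 | *f* = 1.5 |
|---|---|---|---|---|---|
| 5 | 0.1% | 0.8% | 4.8% | 17% | 52% |
| 10 | 2.2% | 0.5% | 3.1% | 18% | 70% |
| 20 | 34% | 3.6% | 2.6% | 25% | 93% |
| 40 | 97% | 21% | 3.2% | 47% | 99.9% |

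The column *f* = 1.0 is the false-signal rate with stable coverage. The artefact is large when counts are high or coverage changes a lot, and when coverage grows. It is slight when counts are low and coverage falls: below *c* = 9 the lower limit is negative, so no single low point can signal. The count itself is still shifted by (*f* − 1) in those cells.

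**4. Inequality.** If a group forms a share *s* of inpatients and is referred exactly as often as everyone else, the ratio of its referrals to those of the rest is *s*/(1 − *s*): 0.11 for *s* = 10%, 0.25 for 20%, 0.43 for 30%. These ratios all describe equal use, so referral numbers alone cannot show inequality or its absence.

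**The case against.** The strongest reply has four parts.

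- **Counts serve a stated purpose.** The VPHC trial is meant to establish the level of use against fixed clinician sessions and a fixed number of appointments, and that is a workload question. This stands: the counts should stay, and rates should be added beside them.
- **There is mitigation.** Ward changes are documented throughout, and the referral form records the ward. This stands in part. The contextual record is meant for interpreting uptake and the running of VPHC, names no adjustment, and is not tied to the ED and Acute Trust numbers.
- **The evaluation is formative and disclaims causal attribution.** True, but the difficulty arises earlier, in the description of uptake itself.
- **A condensed article may leave denominators to a fuller document.** That is fair for the inequality aim, whose scale is open. It is weaker for uptake and monthly attendances, where the article defines the measure as a number, and for uptake does so twice.

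Some stronger readings are tempting but not supported:

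- *Every outcome is a raw count.* Two of the three utilisation items are lengths of stay, the cost section intends a risk, and the inequality aim gives no scale.
- *Changes will show bed numbers and not use.* The article reports no bed figures, so neither the direction nor the share of any such effect is known.
- *The different coverage of VPHC and CC biases a comparison of their uptake.* No such comparison is planned. The only formal contrast between services is of survey scores, and referrals and calls are different units.
- *Fewer attendances would be booked as a false saving.* The threshold analysis asks what effect would be needed for cost neutrality. It does not compute a saving from an observed fall.

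**Conclusion.** The point holds in limited form. VPHC referrals, CC calls and monthly ED or Acute Trust referrals and attendances are defined without a denominator, in a setting where the article itself expects the covered population to change. Movements in these series may partly reflect coverage. The size is unknown. It equals the proportional change in occupied bed-days if use per bed-day is constant, and whether a chart would signal it depends on the count level, with the percentages above resting wholly on assumed Poisson means and bed changes. The inequality aim lacks a named comparison population, which is a gap to close and not evidence of a wrong analysis. This is an inexpensive improvement worth making; it does not invalidate the evaluation.

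**What to change.** 1. Keep the counts of referrals and calls for workload and capacity.
2. Add VPHC referrals, CC calls and ED/Acute Trust referrals and attendances per 1,000 occupied bed-days of the wards with access in that period. Chart them on u-charts instead of count charts. If they are modelled, use a log bed-day offset.
3. Base the before/during comparison, and the baseline risk that enters the threshold analysis, on these rates.
4. State the denominators of the referral rate and of reach. If CC is extended to community teams, report those calls separately, since bed-days do not apply to them.
5. For the inequality aim, compare VPHC referrals by demographic group with each group's share of inpatients or bed-days on the eligible wards, taken from CRIS. Standardising for age and long-term conditions is optional.

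**Cost.** A little more data handling. Occupied bed-days are not listed as a data item, but CRIS, routine SLaM service data and SLaM length of stay are already in the plan and should allow them to be derived. The ward is already recorded on each VPHC referral.

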### Secondary outcomes

Specific outcomes for the VPHC (all routinely recorded):
Number of appointments booked that take place.Reasons given for appointments not attended and any alternative actions taken.Time spent on triage, telephone advice and virtual appointments by the VPHC consultant and ANP.

Specific outcomes for CC (all routinely recorded): referral avoided, referral made, admission avoided, admission made, diagnostics requested.

The CC system asks referrers to document the actions that are taken from the CC call. It should be noted that this is only recorded if the referrer stays on the line after the call to complete this and currently take-up of this is low. If the CC app is used the name of referrer, speciality called, length of time waiting to be connected and length of call is also documented.

*Tertiary outcomes* (for both VPHC and CC, to be collected via self-report):

We will collect feedback from staff on the usability of both services using a questionnaire administered either online or by telephone. The questionnaire will include questions on the following: experiences of using either VPHC or CC, whether using either service was perceived to decrease the time spent on managing physical health compared with previous experiences, any perceived barriers to using either service and any unintended consequences for the patient or the ward in using either service. Participants will also be asked to complete the validated Acceptability Intervention Measure (4 questions), Intervention Appropriateness Measure (4 questions) and Feasibility of Intervention Measure (4 questions) [13]. These measures will offer a standardised assessment of three well-established facets of implementation success, namely how acceptable, appropriate and feasible a new intervention and the manner in which it is being implemented is seen by its intended users [14]. We will consider the feasibility of collecting these scales at regular intervals (e.g. 4-monthly) to allow us to assess longitudinal fluctuations in overall ‘implementability’ of the two interventions as the strategies to support implementation are optimised through the study.

### Implementation data analysis

Contextual factors will be documented throughout roll out such as ongoing changes to SLaM ward configurations in response to infection prevention and control guidelines or any changes to services provided by local Acute Trusts. This contextual data will be used to understand external influences on the uptake of the VPHC and CC and the running of the VPHC.

For our primary implementation assessment, data on implementation strategies applied will be collected and a descriptive analysis conducted, categorised by service (VPHC and CC). The number and type of strategies used will be recorded. Precisely how the strategies were implemented will be described qualitatively and any shifts in strategies over time also recorded.

For our secondary implementation assessment, a descriptive analysis will be conducted for both services for the primary (measured as number of referrals being made for VPHC on a monthly basis and number of calls being made for CC on a weekly basis), secondary (measured as number of appointments, reasons of appointments and access to internal triage) and implementation outcomes. In order to monitor primary and secondary outcomes, descriptive graphs and Statistical Process Control charts will be employed on weekly and monthly basis.

For our tertiary implementation assessment, standardised implementation survey outcomes (AIM, IAM, FIM) will be assessed via a descriptive statistical analysis. Difference in the total scores of implementation survey outcomes by service (VPHC vs CC) and within each service over time (to capture any effects of different implementation strategies) will be assessed with the use of generalised regression models (Poisson or linear depending on the distribution of the outcome).

As the evaluation design is formative, outcomes will be analysed and fed back to SLaM via the Physical Health Implementation Committee and the IMPHS steering group, and this will be provided in an easily understood usage report. This will allow adjustments to be made to the implementation process of both interventions.

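### Poisson regression is allowed for the AIM, IAM and FIM totals, which are bounded sums of four ratings and not counts, so its standard errors would depend on how the items are numbered

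*Protocol article*

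**What the plan says.** The Secondary outcomes section of the protocol article lists, as tertiary outcomes ("for both VPHC and CC, to be collected via self-report"), the "validated Acceptability Intervention Measure (4 questions), Intervention Appropriateness Measure (4 questions) and Feasibility of Intervention Measure (4 questions"). It calls them scales and leaves open whether they will be repeated: "We will consider the feasibility of collecting these scales at regular intervals (e.g. 4-monthly").

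The Implementation data analysis section then states the comparison, "Difference in the total scores of implementation survey outcomes by service (VPHC vs CC) and within each service over time", and the method, "generalised regression models (Poisson or linear depending on the distribution of the outcome"). These are the only two models named.

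The same section assigns the genuine counts, VPHC referrals and CC calls, to descriptive analysis, graphs and Statistical Process Control charts. Within this plan, Poisson therefore applies only to the scale totals.

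The article does not give the response categories, their numbering, an expected mean or SD, a number of respondents, or a variance estimator for these models.

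**The concern.** A Poisson model suits a count of events with no fixed upper limit, and it ties the variance to the mean. A total of four ratings is not of that kind. Its range is fixed by the response format, and its mean moves up or down with the arbitrary number given to the lowest category, while its spread stays the same. The variance that Poisson assumes is therefore partly a product of the numbering.

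Making the choice depend on the observed distribution does not remove the problem. Skewness or bunching near the ceiling does not turn a bounded score into a count, and the plan offers no third option, such as an ordinal model, for that situation.

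At stake are the confidence intervals and p-values for VPHC against CC and for change within each service. The article uses the change over time to look for effects of different implementation strategies, and it feeds outcomes back so that implementation can be adjusted. Intervals of the wrong width could hide a real change or, in the other direction, suggest one that is not there.

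**Working it through.** The article gives no power, sample size, mean or SD for these scores, so there is no figure of its own to reproduce.

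**Inputs**
- From the article: four questions per measure; totals analysed; Poisson or linear regression.
- Assumed, not in the article: five ordered response categories per item, numbered 1 to 5 (total 4 to 20) or 0 to 4 (total 0 to 16); total SD from 2 to 5; 30 ratings per service, independent between services.

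**1. Size of the standard error.** Poisson sets variance = mean, so

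model SE / true SE = √mean / SD.

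| Numbering | Mean | SD 2 | SD 3 | SD 4 | SD 5 |
|---|---|---|---|---|---|
| 1 to 5 | 12 | 1.73 | 1.15 | 0.87 | 0.69 |
| 1 to 5 | 14 | 1.87 | 1.25 | 0.94 | 0.75 |
| 1 to 5 | 16 | 2.00 | 1.33 | 1.00 | 0.80 |
| 1 to 5 | 18 | 2.12 | 1.41 | 1.06 | 0.85 |
| 0 to 4 | 8 | 1.41 | 0.94 | 0.71 | 0.57 |
| 0 to 4 | 10 | 1.58 | 1.05 | 0.79 | 0.63 |
| 0 to 4 | 12 | 1.73 | 1.15 | 0.87 | 0.69 |
| 0 to 4 | 14 | 1.87 | 1.25 | 0.94 | 0.75 |

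The four rows for 0 to 4 describe the same answers as the four rows for 1 to 5, with 4 subtracted from every total.

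**2. Dependence on numbering.** Take one set of answers with SD 3. Numbered 1 to 5 with mean 16, the ratio is 4/3 = 1.33. Numbered 0 to 4 the mean is 12 and the ratio is 3.46/3 = 1.15. Nothing in the data has changed.

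**3. Direction.** The Poisson SE is too wide when SD < √mean. With items 1 to 5 that limit is 3.46, 3.74, 4.00 and 4.24 at means 12, 14, 16 and 18. With items 0 to 4 it is 2.83, 3.16, 3.46 and 3.74 at means 8, 10, 12 and 14. Over SD 2, 2.5, 3 and 3.5 at these means, the SE is too wide in 15 of 16 combinations with items 1 to 5 and in 12 of 16 with items 0 to 4. At SD 4 to 5 it is mostly too narrow.

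**4. Coverage.** At mean 16 and SD 3, a nominal 95% interval covers 2Φ(1.96 × 4/3) − 1 = 2Φ(2.613) − 1 = 99.1%.

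**5. Power (normal approximation).** True difference 2, SD 2.5, mean 16, 30 per service.
- True SE = 2.5 × √(2/30) = 0.645.
- Linear: critical difference 1.96 × 0.645 = 1.265; power = Φ((2 − 1.265)/0.645) = Φ(1.14) = 87%.
- Poisson: critical difference 1.96 × 4 × √(2/30) = 2.024; power = Φ((2 − 2.024)/0.645) = Φ(−0.04), about 48%.

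**6. Simulation check.** Two groups of 30, four correlated five-category items, three levels of spread (total SD about 2.4 to 3.5), 4,000 runs per setting, two-sided 5% test.

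| Quantity | Poisson, items 1 to 5 | Poisson, items 0 to 4 | Linear, both numberings |
|---|---|---|---|
| Rejection with no difference | 0.1% to 2.6% | 0.6% to 6.1% | 4.6% to 5.8% |
| Power, half-point shift per item | 26% to 29% | 36% to 48% | 42% to 86% |

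A log ratio of means with an empirical (robust) variance behaved almost exactly like the linear model.

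**The case against.** The strongest reply has four parts.

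- **The rule is conditional.** Poisson is used only if the distribution supports it. Satisfied users would give left-skewed totals with little spread, which do not look like Poisson data, so a careful analyst may well choose linear. This stands in part. A reader might infer that skewed totals are sent to Poisson, but the article says nothing about skew. What remains is that Poisson is one of only two permitted models and is not a sound choice for these totals in either case.
- **The direction is not established.** A reader might infer that the intervals will always be too wide. The article gives neither the response format nor the spread, and the table shows the reverse at larger SDs, sooner with items numbered from 0. This objection stands in full. Only the lack of a basis for the variance, and its dependence on numbering, are certain.
- **The variance method may be set elsewhere.** A Poisson mean model still estimates the two group means correctly, and a robust or quasi-Poisson variance would repair the standard errors. A fuller analysis plan could state one. That is fair, but the point is not a missing detail: the article names an unsuitable model and says nothing that repairs it.
- **Little depends on it.** The outcomes are tertiary and first analysed descriptively, the evaluation is formative, and the Discussion places causal claims about services and strategies outside its remit. No alpha, sample size or decision rule is stated for these scores. This stands and limits the weight of the point.

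The measures are described as validated, and nothing suggests that the team would renumber the items. Dependence on numbering is evidence that the model is unsuitable; it is not a forecast of what the team will do.

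**Conclusion.** The point holds, with limited impact. Poisson regression is not suitable for the AIM, IAM and FIM totals. That follows from what the totals are and needs no assumed figures beyond a fixed set of response categories per question.

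The size does rest on assumptions. For total SDs of 2 to 3.5 the model SE is 0.99 to 2.12 times the true SE with items 1 to 5, and 0.81 to 1.87 times with items 0 to 4. For SDs of 4 to 5 the ranges are 0.69 to 1.06 and 0.57 to 0.94. The 33% excess and the fall in power from 87% to about 48% illustrate one plausible case and do not predict this study's results. The power figures also assume independent groups, which would fail if the same staff rate both services.

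The documents do not support the stronger conclusion that the evaluation will miss real differences between services. That would require the analyst to choose Poisson, to use its model-based variance, and to find a small spread.

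**What to change.** In the Implementation data analysis section, remove Poisson for these totals. Name linear regression with robust standard errors as the single main model for each measure, clustered by respondent where staff rate both services or answer more than once. Add ordinal (proportional-odds) regression as a sensitivity analysis for ceiling effects. State the item numbering and the range of the total so that readers can interpret the differences.

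The descriptive and control-chart analysis of referrals and calls needs no change. The cost is one clause of wording and slightly more analysis. The questionnaires stay as they are, but clustering needs a pseudonymous identifier that links one respondent's ratings.
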